### Analyses

Descriptive statistics will be used to summarize the distribution of the data. Baseline comparisons between groups will be conducted using the Student *t* tests or chi-square tests, as appropriate, for continuous and categorical demographics, primary, and secondary outcomes. These comparisons will assess the extent to which differences remain between groups at baseline despite randomization. To evaluate the effect of the intervention, intention-to-treat multilevel mixed-effects models will be used. These models will be linear, ordered, or logistic, depending on the characteristics of the data and whether transformations are required. The models will examine the effects of the intervention on each key primary and secondary outcome, incorporating an interaction term between time point (baseline or follow-up) and randomization group (intervention or control). These multilevel analyses will account for the nested structure of the sample and the longitudinal nature of the data, with parents nested within families and repeated measures over time. Individual- and family-level covariates will be included in the models as appropriate. Secondary analyses will assess whether changes in parenting and coparenting practices, and the interaction between these two, predict changes in child health behaviors using multilevel and structural equation modeling. Additionally, dose-response sensitivity analyses with mixed-effect models will evaluate the relationship between the level of exposure/adherence to the intervention (measured via app analytics) and the magnitude of changes in parenting and coparenting practices and child health behaviors. If deemed necessary, imputation techniques will be applied to address missing data. In such a case, the specific imputation method (eg, multivariate multiple imputation, chained equations) will be selected based on variable types and patterns of missingness detected in the data.

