### Sample Size

The sample size calculation for this RCT is based on the primary outcome: parenting practices. The study is designed to achieve 80% power at an α level of 0.05 to detect a group difference of 0.5 points on a 5-point Likert scale (10% change), assuming a SD of 0.8. This 0.5-point difference corresponds to an effect size of Cohen *d* of 0.63, calculated as the mean difference divided by the anticipated SD (ie, 0.5÷0.8=0.63). According to Cohen conventional thresholds, where small effect >0.2, moderate effect >0.5, and large effect >0.8 [44], a *d* of 0.63 represents a moderate effect size. The assumed SD of 0.8 is drawn from secondary data analyses [4,45] of the measurement study that developed the PAPP and FPP item banks, which are the instruments used in this study. Based on this calculation, a minimum of 41 families per group (82 families in total) is required [46]. To account for an anticipated 30% attrition rate and missing data, informed by a previous Canadian study engaging one caregiver per family in an mHealth lifestyle intervention for pediatric obesity [47], we estimate that at least 118 families will be needed for this RCT. Given the additional challenges associated with recruiting a second caregiver and, in particular, fathers [13], the target sample size specifically refers to 2-parent families, defined, for the purpose of this study, as a family where there are 2 caregivers participating in the trial. However, to promote inclusivity and support diverse family structures, one-parent families (ie, families with only one caregiver participating in the trial) will also be eligible to participate and be included in the overall sample (provided that they meet the eligibility criteria) without counting them toward the target sample of 118 two-parent families. Therefore, recruitment will stop once 118 two-parent families have been randomized, which may result in a larger overall sample size.

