### Randomization

Families will be randomly assigned to intervention or waitlist control groups using a computer-generated randomization schedule created via Sealed Envelope [48]. Block randomization will be used with block sizes of 2, 4, and 6, and a 1:1 randomization ratio. The allocation schedule will be securely concealed within the randomization module of REDCap and will only be revealed after all participating caregivers in a family have completed the baseline assessments. To ensure integrity, research team members will not create, access, or modify the allocation schedule, as it will be fully computer-generated. Families will not be blinded to their group assignment because intervention group families will require immediate app access. Similarly, research team members will need to know the families’ group assignments to register them on the mHealth platform and follow up with them if technical issues arise. However, the randomization group will remain concealed from researchers during the data cleaning and analysis stage to minimize bias.

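### For linear outcomes, the time-by-group interaction, read conventionally, forgoes precision that the pre-allocation baseline offers at almost no cost; the estimate itself is unbiased

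*Protocol article*

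**What the plan says.** The Analyses section plans intention-to-treat multilevel models for each primary and secondary outcome, "incorporating an interaction term between time point (baseline or follow-up) and randomization group (intervention or control"). The Measures overview sets two assessments, baseline and about 2 months after randomization. Models may be linear, ordered or logistic. The section does not say whether a group main effect is included or whether the baseline value of the outcome is a covariate.

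The same section plans t and chi-square tests of the arms at baseline on demographics and on primary and secondary outcomes: "These comparisons will assess the extent to which differences remain between groups at baseline despite randomization".

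Under Randomization, allocation "will only be revealed after all participating caregivers in a family have completed the baseline assessments".

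Under Sample Size, the trial is sized "to detect a group difference of 0.5 points on a 5-point Likert scale (10% change), assuming a SD of 0.8", with the standardized effect "calculated as the mean difference divided by the anticipated SD (ie, 0.5÷0.8=0.63"). No baseline to follow-up correlation is given.

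**The concern.** With one baseline and one follow-up, a model containing time, group and time × group fits four free means. Its interaction is the difference between arms in mean change and carries the sampling noise of the baseline difference in full. Because baseline is completed before allocation is known, that difference is chance alone. A model that uses this fact gives the same expected effect with a smaller standard error.

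Two related matters follow. First, the sample size rests on the SD of a single score, which is the SD of a change only at one value of ρ. Second, significance tests of baseline differences ask a question that concealed allocation has already answered. The article gives no firm rule for which covariates enter the models, so nothing prevents those tests from steering the adjustment.

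**Working it through.** **Inputs from the article.** Difference 0.5, SD 0.8, α 0.05, power 80%, 30% attrition (Sample Size); 1:1 allocation (Randomization); two time points (Measures). **Assumed:** ρ, shown over a range; equal variance at both times; linear outcome.

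**1. The plan's own figure.** n per arm = 2 × [0.8 × (1.960 + 0.842) / 0.5]² = 40.2, so 41 per arm and 82 in total. 82 / 0.7 = 117.1, so 118. Both stated figures reproduce with a two-sided test. This calculation compares one score per family at one time.

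**2. Per-arm variance of three contrasts, in units of SD².**
- Follow-up only: 1
- Difference of changes (free baseline means): 2(1-ρ)
- Common baseline mean, or baseline as covariate: 1-ρ²

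The third divided by the second is (1+ρ)/2, so the relative reduction is (1-ρ)/2.

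**3. With attrition.** Let a fraction f of families complete, with baseline-only families kept by maximum likelihood and data missing at random. The free-means variance is (1-ρ²)/f + (1-ρ)² and the constrained variance is (1-ρ²)/f. The reduction is (1-ρ)² / [(1-ρ²)/f + (1-ρ)²], which returns (1-ρ)/2 at f = 1. Example at ρ = 0.5, f = 0.7: 0.25 / (0.75/0.7 + 0.25) = 0.25 / 1.321 = 19%.

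**4. Results.** Power is for 41 completers per arm with one score per family (normal approximation; a t-based calculation gives up to about one point less).

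| ρ (assumed) | Lower variance, complete data | Lower variance, 30% attrition | Power, difference of changes | Power, baseline constrained |
|---|---|---|---|---|
| 0.3 | 35% | 27% | 67% | 84% |
| 0.4 | 30% | 23% | 73% | 87% |
| 0.5 | 25% | 19% | 81% | 90% |
| 0.6 | 20% | 15% | 89% | 94% |
| 0.7 | 15% | 11% | 95.5% | 97.7% |

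Over a wider range with complete data, the reduction is 40% at ρ = 0.2 and 5% at ρ = 0.9.

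**5. Two parents per family.** The complete-data figures are unchanged if the covariance between parents across time scales with ρ. They are smaller if parents share a stable family intercept: 19% instead of 25% at ρ = 0.5 with a within-family correlation of 0.3.

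**6. The SD.** The SD of change is 0.8 × √(2(1-ρ)). It equals 0.8 only at ρ = 0.5; at ρ = 0.4 it is 0.876 and at ρ = 0.3 it is 0.947. Below 0.5, the difference of changes is noisier than the contrast that was sized.

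**7. What the actual sample does to power.** The Results section reports 121 + 62 = 183 families. If all were randomized and 30% are lost, 183 × 0.7 / 2 is about 64 per arm. The difference of changes, one score per family, then has 85% power at ρ = 0.3 and 90% at ρ = 0.4. Alternatively, at 41 per arm, averaging two parents whose changes correlate 0.3 (assumed) multiplies the variance by (1 + 0.3)/2 = 0.65 and gives 84% and 89%.

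**The case against.** The strongest objection is that the article never states free baseline means. A constrained model also contains a time × group term and differs only in leaving out the group main effect, a detail that an analysis plan may settle. That stands as a limit on certainty: the free-means model is an inference. It is the usual reading of the wording, however, and planned tests of baseline outcome differences do not suggest a common baseline mean. If the constraint was intended, one sentence confirms it.

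A reader might infer that the trial is underpowered, at 67% or 73% for ρ of 0.3 or 0.4. The documents do not support this. Those figures count one score per family and 41 families per arm, while the models use both parents and the sample includes one-parent families beyond the target. On the illustrative assumptions in the working, either of these alone restores more than 80%. At ρ of 0.5 or above there is no material shortfall even on the narrow basis.

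A reader might also infer that the baseline tests choose the covariates, or that they have inflated error because parents in a family are paired. The Analyses section states neither such a use nor the unit of testing. What stands is that the tests serve no purpose and should not acquire that one.

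Finally, the variance formula is exact for linear models only. The ordered and logistic models that the plan allows will not show the same figures, so a loss on every outcome cannot be claimed.

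**Conclusion.** The point holds as a matter of efficiency. Under randomization the planned interaction estimates the effect without bias, so this is not an error in the analysis. If baseline means are left free, the variance of the effect on a linear outcome is larger than it need be. Using the baseline fully would lower it by 15-30% for assumed ρ of 0.4 to 0.7 with complete data, by about 11-23% under the planned 30% attrition with baseline-only families retained, and by somewhat less if parents share a stable family intercept. The direction holds for every ρ below 1; the size depends on a correlation that the article does not give. The mismatch between the single-score SD and the SD of change matters only if ρ is below 0.5, and second parents and the additional one-parent families offset it.

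**What to change.** - State whether the models include a group main effect. For linear outcomes, omit it and keep time and time × group, so that the arms share one baseline mean; or model the follow-up score with the baseline score as covariate.
- For ordered and logistic outcomes, model follow-up with the baseline value as covariate.
- Replace the baseline t and chi-square tests with descriptive summaries by arm. Name the covariates in advance, and do not let observed baseline differences select them.
- Record the choice, with its date, while group is still concealed from the analysts as the Randomization section provides.

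The cost is one line of model specification and a dated note; no new data or families are needed. Because the Results section reports that cleaning and analysis have been under way since May 2025, the change must be documented openly as a late decision. If results by group are already known, the planned model should remain the primary one and the constrained model be reported beside it, labelled as added later.

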### Measures

#### Overview

Data collection will occur at baseline and follow-up (approximately 2 months after randomization) for all variables listed below except for sociodemographic variables, which will be evaluated only at baseline. Participants will complete all surveys online using REDCap.

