#### Primary Outcomes

Parenting practices related to nutrition and activity will be measured with items modeled after the validated food [64] and physical activity [65] parenting item banks designed for 5- to 12-year-olds, with some questions adapted for younger children (eg, the original item asks “how often do you have your child help prepare dinner meals”), while the adapted item will ask “how often do you involve your child in simple food tasks when preparing meals (eg, help wash vegetables, arrange the vegetables). Both item banks were informed by parenting and obesity experts and have been evaluated for construct validity (ie, designed to capture the 3 parenting domains of control, structure, and autonomy promotion) related to nutrition and active play. These item banks have shown strong psychometric properties, including measurement invariance by parent gender, making the comparisons valid between mothers and fathers, and Cronbach α ranging from 0.67 to 0.96 [64-67]. Additional items on food, physical activity, and media parenting practices were developed for this study to align with the intervention content. Accordingly, we will assess and report on the psychometric properties of the parenting measurement tools used in this RCT, focusing on construct validity (via factor analysis) and reliability (via Cronbach α). Reassessing these properties in the final sample will provide a more accurate evaluation of the validity and reliability of the measures applied in this trial.

Coparenting practices will be evaluated with items adapted from the Agreement subscale of the Coparenting Relationship Scale [17], designed for children aged 6 months to 3 years and further used with children up to 7 years old [18,68]. The scale shows adequate psychometric properties, including construct validity and reliability (Cronbach α ranging from 0.67 to 0.74). The questions will inquire about the level of agreement between key caregivers regarding their expectations, goals, approaches, and conceptions about their child’s lifestyle behaviors. Additionally, coparenting practices will be examined in 2-parent families by comparing the parenting practice scores of both parents/caregivers within the family.

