#### Secondary Outcomes

Child eating behaviors will be evaluated with the Child Eating Behavior Questionnaire [69], examining child emotional overeating, food responsiveness, food fussiness, and satiety responsiveness. This instrument, designed for children aged 2-9 years, has been extensively used, showing adequate psychometric properties, including Cronbach α ranging from 0.72 to 0.91 [69]. In addition, parents will be asked to report on the number of days per week that their child consumes key food markers (ie, fruit and vegetables, fruit juice and sugary drinks, sweet and salty treats), with questions adapted from the Canadian Community Health Survey [70] and the Center for Diseases Control’s Behavioral Risk Factor Surveillance System Questionnaire [71] and National Youth Physical Activity and Nutrition Study [72].

Child active and outdoor play will be measured with questions from the instrument designed by Burdette et al [73] for young children. The questions inquire about the number of minutes per day and the number of days per week that the child engages in active and outdoor play on a regular weekday and weekend day.

Children’s screen time will be measured by inquiring about the number of days in the previous week that children spent more than 1 hour/day in front of screens, when counting all screen-media devices (eg, TV, computer, tablet, and smartphone).

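### Caregiver reports supply both sides of the parenting-to-child-behaviour analysis, so reporting error that shifts between surveys can create an association; a cross-reporter sensitivity model would expose much of it

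*Protocol article*

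**What the plan says.** All statements are in the protocol article.

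- **Analyses:** the secondary analyses ask whether change in parenting, change in coparenting and their interaction "predict changes in child health behaviors using multilevel and structural equation modeling". The intervention-effect models in the same section treat parents as nested within families. The text does not say whose report of the child is paired with whose report of practices.
- **Measures, Overview:** "Participants will complete all surveys online using REDCap".
- **Primary Outcomes (predictor side):** parenting practices are self-reported, for example "how often do you involve your child in simple food tasks when preparing meals". Coparenting agreement is also self-reported: "The questions will inquire about the level of agreement between key caregivers". In two-parent families, coparenting is additionally examined by comparing the two caregivers' practice scores.
- **Secondary Outcomes (outcome side):** for diet, "parents will be asked to report on the number of days per week that their child consumes key food markers". Eating behaviour, active and outdoor play, and screen time are questionnaire items too.
- **Randomization:** "Families will not be blinded to their group assignment".
- **Intervention Group and Exposure/Adherence:** app analytics are the only objective data. They measure exposure and enter neither side of this analysis.
- **Strengths and Limitations:** short duration and lack of long-term follow-up are named; shared reporter error is not.

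**The concern.** Taking change scores cancels a caregiver's stable reporting style. It does not cancel error that moves between the two surveys, such as a shift in mood, optimism or the wish to show progress. If the same person reports both practices and child behaviour, such a shift moves both change scores together. Knowing the arm and having been taught which practices and habits are desirable make shifts of this kind plausible.

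A family random effect does not remove error covariance within one person, and neither does adjusting for arm. A structural model removes it only if the covariance is modelled, for example through a second informant or a method factor; the article describes neither. What is at stake is the reading of a positive result: a significant link between better parenting and healthier child behaviour could be partly or wholly a reporting artefact. Two-parent families already supply a second report that could help tell the two apart.

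**Working it through.** **The plan's own figures.** No figure is given for this analysis. The sample size reproduces and is not in dispute: 0.5/0.8 = 0.625; 2 × (1.96 + 0.84)² / 0.625² ≈ 40.1, rounded up to 41 per group, 82 in total; 82/0.70 = 117.1, rounded up to 118.

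**Inputs from the documents.** 121 two-parent and 62 one-parent families (Results); 30% anticipated attrition and missing data (Sample Size). Two-parent families expected at follow-up: 121 × 0.70 = 84.7, taken as 85, or 170 caregiver records.

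**Assumed inputs.** Change-score reliability *R* from 0.4 to 0.8, equal on both sides. Correlation *e* from 0.1 to 0.4 between one caregiver's error in practice change and the same caregiver's error in child change.

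**Formula.** With no true link, the induced correlation is *e* × (1 − *R*).

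**Simulated rejection at nominal 5%** (85 families, no true link; for *R* = 0.4 and 0.6, 1,500 runs per setting with family-clustered standard errors; the *R* = 0.8 row is a separate rerun for three values of *e*). Induced correlation in brackets.

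| *R* | *e* = 0.1 | *e* = 0.2 | *e* = 0.3 | *e* = 0.4 |
|---|---|---|---|---|
| 0.4 | 14% (0.06) | 35% (0.12) | 64% (0.18) | 86% (0.24) |
| 0.6 | 9% (0.04) | 18% (0.08) | 33% (0.12) | 51% (0.16) |
| 0.8 | 7% (0.02) | 8% (0.04) | not run | 17% (0.08) |

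Settings with equal induced correlation give nearly equal rates (0.04: 9% and 8%; 0.08: 18% and 17%; 0.12: 35% and 33%).

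**Hand check.** Fisher's z with 170 records, ignoring clustering. At 0.24: 0.245 × √167 = 3.16, and Φ(3.16 − 1.96) ≈ 0.88, against 86% simulated. At 0.04: 0.040 × √167 = 0.52, giving about 0.08, against 9%.

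**Second parameterisation.** Let *s* be the share of each change score's variance that is error common to both reports, with one record per family. For *s* = 0.05, 0.10, 0.20 and 0.30, rejection is 7%, 15%, 44% and 79% with 82 families, and 9%, 20%, 62% and 93% with 128 families (183 × 0.70). With arm in the model, the simulated rate at *s* = 0.20 is still 43–46% with 82 families and 61–63% with 128.

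**Cross-reporter pairing.** If the two caregivers' errors are independent, rejection is 5–7% in the 85-family simulation and 4–6% in the second. If they correlate 0.3, it is 6–16% and about 6–17% respectively. At *R* = 0.4 and *e* = 0.4, with partner error correlation of 0.3 to 0.5, it reaches 14–29%.

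**The case against.** **The pairing is not stated.** A reader might infer that the protocol prescribes same-caregiver pairing or declines to use the second report. It does neither. It gives this analysis one sentence, and a structural model could take both parents' reports. An article may leave that detail to an analysis plan. This stands, and it limits the point to what the described data can support.

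**One coparenting measure already uses two reporters.** The within-family comparison of practice scores draws on both caregivers. This stands as a partial exception: the score still contains the error of whichever caregiver reports the child.

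**The trial's main claims do not rest here.** Purpose and Hypothesis is framed as a comparison between arms, and this analysis is secondary. This stands. A reader might infer that the randomised result is compromised; this mechanism does not reach it, although unblinded self-report can bias that comparison separately.

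**The reliability range is not anchored in the documents.** One might derive it from "Cronbach α ranging from 0.67 to 0.74". With (α − *r*)/(1 − *r*) and an assumed correlation *r* of 0.4 to 0.5 between the two surveys, that gives 0.34 to 0.57. But those values belong only to the Agreement subscale. The child eating scales reach 0.91 (change reliability 0.82 to 0.85) and the parenting item banks 0.96 (0.92 to 0.93). More fundamentally, alpha treats a mood shift that moves all items together as reliable variance, so it does not measure this error. This stands: the size is an assumption, and 86% is the worst corner of the grid.

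**The cross-reporter model is imperfect and weak.** Partners share an arm and are encouraged to set goals together, so their errors may correlate. Power is also low: with a true correlation of 0.3 and 85 families, about 22% at reliability 0.4 and 44% at 0.6. This stands, and it rules out treating agreement between the two models as a condition for any conclusion.

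**Conclusion.** The point holds as a limit on a secondary analysis. With caregiver surveys on both sides and respondents who know their arm, shared reporting error that changes between surveys can yield an association when there is none, and neither a family random effect nor arm adjustment removes it. The same-reporter condition is certain for the 62 one-parent families and probable, not stated, for the two-parent families.

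Under the assumed ranges, the false-positive rate runs from roughly 7%, close to nominal, to 86%. Nothing in the documents locates the trial within that range. The supportable conclusion is that a same-reporter association alone cannot be separated from shared error, not that a positive finding would be false.

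**What to change.** In two-parent families, add a sensitivity model relating each caregiver's change in practices to the other caregiver's report of the child's change. Fit both directions together with a family random effect, adjusted for randomised arm and baseline values. Report it beside the same-reporter model. Describe a same-reporter association without cross-reporter support as possibly due to shared reporting error, and name this among the limitations. Do not make agreement in size a binding rule: shared error inflates the same-reporter estimate and the cross-reporter test has little power, so real links would often fail it.

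The cost is one further model on data already collected. One-parent families, and families with a single respondent at follow-up, drop out of it, and its intervals are wider. Correlated errors between partners leave some bias. The Results section places the trial in data cleaning and analysis as of October 2025, so the model should be specified before this analysis is interpreted, with the date of the addition stated.
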